
#### Electromyography

Three EMG setups will be utilized in the project. The first setup will be used for the strength, ankle flexibility and neural tests (i.e. H-reflex, PAD and tonic stretch reflex threshold). EMG activity will be recorded from Sol, MG and TA muscles with self-adhesive electrodes (Blue Sensor N, Ag/AgCl, 0.28 cm^2^; Ambu, Ballerup, Denmark), and a ground electrode placed on the tibia. Electrode placement and skin preparation will be performed according to SENIAM [85]. The electrodes will be placed on the muscle belly in accordance with the underlying fiber direction (20-mm-interelectrode distance). EMG signals will be amplified and high-pass filtered (1000X, 10 Hz) by a preamplifier (NL824; Digitimer, Welwyn Garden City, UK) and then band-pass filtered (10 Hz to 1 kHz) by a differential amplifier (NL900D/NL820A; Digitimer Ltd., UK). The signals will be acquired on a personal computer at a rate of 5 kHz via a 16-bit A/D converter (CED power 1401; Cambridge Electronics Design, Cambridge, UK). EMG during the maximal voluntary plantarflexion and dorsiflexion trials will be quantified in 200 ms root mean square (RMS) windows preceding the joint angles of 0°, 5.5°, 11°, 16.5°, 22° and 27.5°. TA coactivation during plantarflexion will be expressed as % of the maximal RMS EMG obtained on the dorsiflexion trial at the same joint position. The same procedure will be performed to express Sol and MG coactivation during ankle dorsiflexion.

The second setup utilizes a wireless EMG system (Noraxon, Scottsdale, USA) that will acquire EMG activity during the instrumented gait analysis. Data acquisition configuration, muscles tested, and electrode placement are identical to setup 1, except for two differences: 1) sampling frequency is 1.5 kHz; 2) two sets of bipolar electrodes will be placed in TA muscle, 8–10 cm apart depending on the subject’s tibia length.

The third EMG setup is built-in the MEG System (Elekta Neuromag TRIUX, Elekta Oy, Helsinki, Finland). The same bipolar electrode placement as in setup 2 will be utilized, with a MEG compatible electrode (Neuroline 720, Ag/AgCl, 0.28 cm2; Ambu, Ballerup, Denmark). EMG signal will be sampled at 1 KHz and band-pass filtered 1–1000 Hz.

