#### Magnetoencephalography (MEG)

Participants will be seated inside a magnetically shielded room (VACOSHIELD, Vacuumschmelze GmbH & Co. KG, Hanau, Germany) with their heads positioned within the sensor array of the whole-head-MEG System (Elekta Neuromag TRIUX, Elekta Oy, Helsinki, Finland), consisting of 204 planar gradiometers and 102 magnetometers. MEG data will be acquired at 1000 Hz and band-pass filtered (0.1–330 Hz).

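### The EMG recorded with MEG (setup 3) is given a 1000 Hz upper cutoff at 1 kHz sampling, twice the 500 Hz limit; setup 2 may share the fault in milder form

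*Protocol article*

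**What the plan says.** The Electromyography section of the protocol article describes three recording setups.

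- **Setup 1** (strength, ankle flexibility and reflex tests). The signal is "then band-pass filtered (10 Hz to 1 kHz) by a differential amplifier". The rate is given separately: "The signals will be acquired on a personal computer at a rate of 5 kHz".
- **Setup 2** (wireless, instrumented gait analysis). No filter band of its own is stated. The text says: "Data acquisition configuration, muscles tested, and electrode placement are identical to setup 1, except for two differences". One of the two differences is "sampling frequency is 1.5 kHz"; the other is a second electrode pair on tibialis anterior.
- **Setup 3** (built into the MEG system): "EMG signal will be sampled at 1 KHz and band-pass filtered 1–1000 Hz".

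The Magnetoencephalography section says of the MEG channels of that same system: "MEG data will be acquired at 1000 Hz and band-pass filtered (0.1–330 Hz".

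The Neural parameters section takes gait intramuscular coherence (condition A) from setup 2. It takes cortico-muscular and intramuscular coherence during isometric dorsiflexion (condition B) from setup 3. In both conditions the EMG is full-wave rectified before coherence is computed. Hypotheses m and n in the Study purpose section rest on these two conditions.

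**The concern.** A signal sampled at rate fs is represented correctly only if it has been limited to frequencies below fs/2 beforehand. Setup 3's stated upper cutoff equals its sampling rate, so the filter as described gives no protection between 500 and 1000 Hz. Energy there would reappear at false frequencies across the whole recorded band and could not be separated out offline.

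Coherence is a spectral measure, so a wrong band matters more here than for a simple amplitude summary. Setup 3 is the only source for condition B. At stake are hypothesis m and the isometric part of hypothesis n; if setup 2 has the same fault, the gait part of n is touched as well. A reader trying to reproduce the recording also cannot tell whether the settings are wrong or only their description.

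**Working it through.** **Inputs.** Sampling rates and upper cutoffs come from the Electromyography, Physical activity (EMG shorts) and Magnetoencephalography sections.

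**Check 1: cutoff against fs/2.** Content at a frequency f between fs/2 and fs reappears at fs − f.

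| Recording | fs (Hz) | fs/2 (Hz) | Stated upper cutoff (Hz) | Result |
|---|---|---|---|---|
| Setup 1 | 5000 | 2500 | 1000 | consistent |
| Setup 2 (band by reference) | 1500 | 750 | 1000 | 750–1000 folds to 500–750 |
| Setup 3 | 1000 | 500 | 1000 | 500–1000 folds to 0–500 |
| MEG channels | 1000 | 500 | 330 | consistent |
| EMG shorts | 1000 | 500 | 200 | consistent |

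For setup 3, 1000 − 500 = 500 and 1000 − 1000 = 0, so the folded content covers the entire usable band. For setup 2, 1500 − 750 = 750 and 1500 − 1000 = 500, so it stays at 500–750 Hz and reaches low frequencies only through rectification.

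**Check 2: how much energy could fold (assumed spectrum).** The article gives no EMG spectrum. A common model shape is P(f) = fh⁴f² / [(f² + fl²)(f² + fh²)²]. Shares of power over 1–1000 Hz:

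| fl, fh (Hz) | 500–1000 Hz | 750–1000 Hz |
|---|---|---|
| 60, 120 | 1.1% | 0.2% |
| 60, 200 | 3.3% | 0.7% |
| 80, 300 | 8.5% | 2.0% |

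**Check 3: effect on rectified coherence (simulation, assumed inputs).** 480 s of EMG (the article's condition B length), two channels, an assumed shared 15–30 Hz drive, rectification, 1 s sections, mean coherence over 15–30 Hz. The comparison is no anti-alias filter against a filter below fs/2.

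Without added noise:

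| Spectrum | 1 kHz: unfiltered vs filtered | 1.5 kHz: unfiltered vs filtered |
|---|---|---|
| 60, 120 | 0.424 vs 0.415 | 0.427 vs 0.424 |
| 80, 300 | 0.591 vs 0.549 | 0.619 vs 0.599 |

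The differences run from 0.427 − 0.424 = 0.003 to 0.591 − 0.549 = 0.042, all upward. This is plausible: folded EMG carries the same amplitude modulation as the rest of the EMG.

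A separate run at 1 kHz added flat independent noise. Its noise-free baselines differ slightly from those above, so compare within rows.

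| Noise (share of EMG power) | fh 120 | Change | fh 300 | Change |
|---|---|---|---|---|
| 0 | 0.450 vs 0.442 | +2% | 0.616 vs 0.577 | +7% |
| 5% | 0.413 vs 0.424 | −3% | 0.559 vs 0.550 | +2% |
| 10% | 0.384 vs 0.410 | −6% | 0.520 vs 0.528 | −2% |
| 30% | 0.280 vs 0.345 | −19% | 0.366 vs 0.441 | −17% |

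Change is unfiltered/filtered − 1; for example 0.280/0.345 − 1 = −19%. The sign turns with noise and spectrum. The shift is a few percent in clean recordings and becomes large only at a noise level that would already be poor.

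**The case against.** **Actual aliasing is not shown.** The stated band may be nominal. Setup 3 is part of a recorder whose MEG channels are limited to 330 Hz, and its EMG channels may be limited too; the wireless system may also filter internally. This stands. The fault lies in the specification, and the remedy may be no more than a corrected figure.

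**Setup 2's band is an inference.** It is carried over by reference from a wired amplifier to a different wireless system, and the sentence may not have been meant to cover the filter. This also stands, so setup 2 is only a conditional, secondary part of the point.

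**A reader might infer a definite loss of coherence.** With noise at 5–10% of EMG power, doubling it and applying [S/(S+N)]² gives (1.05/1.10)² = 0.91 and (1.10/1.20)² = 0.84, a loss of 9–16%. The documents do not support this. The formula is for linear coherence between two noisy channels, whereas the article rectifies first; cortico-muscular coherence has only one EMG channel; and the noise level is assumed. The simulations give smaller shifts at those noise levels and no fixed sign.

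**A reader might also infer that a strength gain alone would raise coherence**, because condition B is recorded at 10% of maximum and a stronger signal sits further above the noise. Any noise floor has that effect, with or without aliasing. In the simulation, a fall in noise from 30% to 5% raises coherence by 0.13–0.19 unfiltered (0.413 − 0.280; 0.559 − 0.366) and by 0.08–0.11 filtered (0.424 − 0.345; 0.550 − 0.441). Aliasing would enlarge the dependence under those assumptions, but the article documents no noise level or change in noise. It remains a possibility, not a finding.

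**Conclusion.** The point holds for setup 3 as written: the stated cutoff is 1000 Hz where the sampling rate allows less than 500 Hz. Every other pairing that the article states outright respects the limit, including the MEG channels on the same system at the same rate. That makes it a wrongly stated figure rather than detail left to a fuller document. For setup 2 it holds only if the reference to setup 1 is meant to include the filter band, and then in milder form (1000 Hz against 750 Hz).

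The consequence is probably small and cannot be signed from the documents. The simulated changes rest on an assumed EMG spectrum, an assumed shared drive and assumed noise, and show a range of possibilities rather than an estimate for this trial. Only hypothesis m and hypothesis n are touched, the gait part of n only conditionally. The six-minute walk test and the sample size are unaffected. Severity: minor.

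**What to change.** 1. Check the filter settings actually used for EMG in setups 2 and 3, including any anti-alias filter built into the recorders.
2. If the hardware already limits EMG below half the sampling rate, correct the stated band for setup 3 and state setup 2's band explicitly instead of by reference. The cost is one or two corrected figures.
3. If the low-pass really is 1000 Hz, set it below 500 Hz for setup 3 and below 750 Hz for setup 2, or sample EMG above 2 kHz. Keep one setting per participant across all visits, since a change of cutoff can itself shift coherence, and flag recordings made under the old setting when the coherence results are reported.

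Recruitment is described as running from May 2017 with an expected end in December 2020, so many recordings may already exist. For those, step 3 reduces to disclosure and flagging, because folded content cannot be removed afterwards. The cost is a setting change for new participants and possibly two acquisition settings in the coherence dataset.

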#### Neural parameters

H-reflexes and M-waves will be evoked in Sol by percutaneous electrical stimulation of the tibial nerve, while the participant lies in prone position. A single rectangular pulse (1 ms) will be delivered from a constant-current stimulator (DS7AH; Digitimer, UK). A circular cathode with a pickup area of 0.77 cm^2^ (Unilect4535M, Ag/AgCl; Unomedical, Redditch, UK) will be placed over the tibial nerve on the popliteal fossa, and an oval-shaped, 5.1 × 10.2 cm anode (V-trodes; Mettler Electronics, Anaheim, CA) will be placed above the patella. The stimulation site providing the greatest amplitude of evoked responses in Sol will first be located by a handheld cathode electrode that will be later replaced by a self-adhesive electrode. The full recruitment curve will be attained by starting with a stimulation intensity of 3 mA and increasing in 0.5–2 mA steps (i.e. smaller steps closer to the maximum H-reflex) at 0.1 Hz until the Maximal M-wave is reached. Peak-to-peak values for maximum H-reflex and M-wave will be computed.

The PAD protocol will be performed after the recruitment curve with the participant in the same position. Stimulation intensity will be first adjusted to evoke H-reflex responses corresponding to 75% of maximum H-reflex at 0.1 Hz, then sixteen stimuli at two frequencies (0.1 and 1 Hz) will be performed. H-reflexes will be normalized by the preceding M-wave, and PAD will be computed as the ratio between 1 Hz and 0.1 Hz (i.e. greater values means less PAD). This normalization procedure is important because the H-reflex is directly influenced by the preceding M-wave (i.e. effective stimulation intensity). However, since the stimulation intensity is constant and supposedly so is the preceding M-wave, previous studies [86, 87] have chosen to report the ratio between the absolute peak-to-peak H-reflex values. Thus, for comparison purposes the absolute PAD ratio will also be calculated.

Stretch hyperreflexia of Sol and MG will be assessed utilizing the TSRT [88, 89]. The participant will be seated with the knee joint fully extended and the ankle dynamometer previously described will induce stretches (from 20° of plantarflexion to 0°) on triceps surae at four different velocities: 50, 100, 200 and 300°/s. The stretch velocities will be delivered in a pseudo-randomized and balanced order, yielding 10 stretches in each velocity, with an interval of 2.6–2.9 s. EMG data will be used to determine the joint angle in which the stretch reflex onset occurred (i.e. dynamic stretch reflex threshold, DSRT). A regression line based on a first-order linear equation using all DSRT will be calculated on a stretch velocity-joint angle plot. From the equation, the coefficient of determination, slope and intercept with the x-axis will be attained. The TSRT is the angle at which the regression line intersects with the x-axis, larger values indicate a high level of stretch hyperreflexia. TSRT will be calculated separately for each muscle. In addition to the already established TSRT calculation, we propose using the latency of the H-reflex to take into account the time between the stretch reflex onset and the EMG burst onset. A typical H-reflex latency of 35 ms and a stretch velocity of 300°/s can cause a difference of 10.5° between the stretch reflex and EMG onset, provoking a systematic error towards higher velocities. Thus, all variables in the TSRT will be calculated with and without the latency correction, and the differences will be discussed. Participants will be instructed to relax and will be wearing noise blocking headphones. Trials with EMG exceeding 5% of the isometric plantarflexion MVC in the 500 ms preceding the stretch will be discarded. The EMG burst onset will be defined as a 3SD increase in the RMS of a 20 ms moving average for at least 20 ms compared to the pre-stretch state. Visual inspection of false positives due to small brief muscle activations will be performed and automated onset detection algorithms may also be utilized. H-reflex, PAD and TSRT will be assessed on the most affected limb of the CP group and in the same leg of the age/sex matched control.

Frequency domain analysis of the EMG will be performed in the following conditions: A) intramuscular TA coherence during the swing phase of gait; B) cortico-muscular and intramuscular TA coherence during a sustained isometric ankle dorsiflexion. Condition A will be collected with EMG setup 2, during the instrumented gait analysis test (S2), and B will be collected in the MEG session (S3), using EMG setup 3. Surface EMG will be preprocessed using full-wave rectification as it has been shown to be appropriate for low force muscle actions [90–92]. The finite Fourier Transform using the method of disjoint sections will be utilized [93], in which the complete EMG record R (i.e. approximately 60 s for A, and 480 s for B) is divided in L non-overlapping disjoint sections of length T, where R = LT. For A, T will be selected to reach a spectral resolution ≤5 Hz. If possible, the swing phase will be divided into two or three parts, depending on the actual length of these phases and the achieved frequency resolution. For B, R = 480 s and T = 1 s, yielding a frequency resolution of 1 Hz. The coherence between two rectified EMG signals (x and y) is defined as their cross-spectrum normalized by the auto-spectra for a given frequency (λ), according to the following equation:
$$ {\left|{R}_{xy}\left(\lambda \right)\right|}^2=\frac{{\left|{f}_{xy}\left(\lambda \right)\right|}^2}{f_{xx}\left(\lambda \right){f}_{yy}\left(\lambda \right)} $$

Coherence measures how closely two signals are related by a linear transformation [93, 94], providing a bounded and normative measure of association, taking values between 0 and 1. A perfect linear relationship has a value of 1, while full independence has a value of 0. Pooled coherence estimates will be calculated to characterize both control and experimental groups [95]. The estimation of pooled coherence joins separate signals from different subjects into a single longer signal, and then calculates the coherence of this record using the periodogram approach. Pooling the EMG signal of different participants may result in a non-constant standard deviation (i.e. nonstationarity) between the different sections, in this case signals will be normalized to have unit variance [96].

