**Passive ankle dorsiflexion test**	
Ankle angle < 18° with knee at 0° and 90° = short Soleus muscle.	
Ankle angle < 18° with knee at 0° and ankle angle > 18° with knee at 90° = short Gastrocnemius muscle.	
Ankle angle **>** 18° in with knee in 0° and 90° = good triceps surae flexibility.	
References: [102, 103].	

*ASIS* anterior superior iliac spine. Hip measurements 1–2: 0° = anatomical position, positive values = hip flexion. Knee measurements: 0° = knee in full extension. Ankle measurements: 0° = sole of the foot at right angles to the tibial axis, positive values = dorsiflexion

Neuromechanical responses during the TSRT protocol (i.e. 40 stretches at 4 velocities) will also be analyzed. The higher stretch velocities in this protocol will result in reflex muscle activation, thus involving both passive and active elements. First, mechanical artifacts at the beginning and end of each stretch will be removed, then peak and mean torque, joint stiffness and energy will be calculated for each stretch. Additionally, maximum EMG RMS (EMG setup 1) will be calculated with a 50 ms moving window for each stretch. Comparisons between velocities and between the first and last group of 8 stretches will be performed to gain insight into the differences in neuromechanical responses to dynamic repetitive stretching.

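### The TSRT regression does not name its dependent variable, and the natural reading (velocity regressed on onset angle) makes the threshold move with the scatter of reflex onsets

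*Protocol article*

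**What the plan says.** In the protocol article, under Neural parameters, the dynamometer stretches the calf muscles through 20°, "on triceps surae at four different velocities: 50, 100, 200 and 300°/s", "yielding 10 stretches in each velocity". For the response, "EMG data will be used to determine the joint angle in which the stretch reflex onset occurred"; this angle is the DSRT. A first-order line "using all DSRT will be calculated on a stretch velocity-joint angle plot". R², the slope and the x-axis intercept are taken from the equation, and "The TSRT is the angle at which the regression line intersects with the x-axis". The calculation is done separately for soleus and medial gastrocnemius.

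The section also proposes to allow for reflex latency, on the ground that 35 ms at 300°/s amounts to 10.5°. It commits to this: "all variables in the TSRT will be calculated with and without the latency correction, and the differences will be discussed".

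TSRT is named in secondary hypothesis k (no change expected) and falls under aim 3, the CP–TD comparison of all variables (both in Study purpose).

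**The concern.** An x-intercept that is an angle means angle on the x-axis and velocity on the y-axis. The ordinary equation for that plot is velocity = a + c·angle, with TSRT = −a/c. But velocity is fixed by the device, and the error lies in the angle, which depends on detecting an EMG onset. Least squares with the error-prone variable as predictor flattens the fitted line, and the extrapolation to zero velocity goes too far.

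Two things are at stake. First, two visits or two groups with the same true threshold line but different onset scatter would get different TSRT values. Second, the latency correction is latency × velocity, which is zero at zero velocity. A TSRT difference with and without it could therefore be produced by the direction of the fit and be discussed as if it were physiological.

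**Working it through.** **The plan's own figure.** 0.035 s × 300°/s = 10.5°, as stated.

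**Inputs from the article.** Velocities 50, 100, 200 and 300°/s, 10 stretches each, 40 in all before discards.
- Mean velocity = 650/4 = 162.5°/s.
- Variance = (112.5² + 62.5² + 37.5² + 137.5²)/4 = 9218.75, so SD = 96.0°/s.

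**Inputs not in the article, so assumed.** The threshold slope b (degrees per °/s), the onset SD and hence R².

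**Formulas.** Let angle = α + b·v + error, so the true TSRT is α.
- Angle regressed on velocity, read at v = 0: mean(angle) − b·mean(v) = α.
- Velocity regressed on angle: fitted slope R²/b, so x-intercept = mean(angle) − b·mean(v)/R².
- Size of the difference: |b| × 162.5 × (1 − R²)/R².

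**Size of the shift.** A change of 5° over 50–300°/s is b = 5/250 = 0.02, and |b| × 162.5 = 3.25. A change of 10° is b = 0.04, giving 6.5.

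| R² | (1 − R²)/R² | 5° change | 10° change |
|---|---|---|---|
| 0.9 | 0.111 | 0.4° | 0.7° |
| 0.8 | 0.25 | 0.8° | 1.6° |
| 0.7 | 0.429 | 1.4° | 2.8° |
| 0.5 | 1 | 3.3° | 6.5° |
| 0.3 | 2.333 | 7.6° | 15.2° |

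**Simulation check** (40 stretches, 3000 runs, true TSRT 5° of plantarflexion, 5° change). Velocity-on-angle medians were 4.7, 4.2, 1.9 and −2.1° of plantarflexion at R² 0.9, 0.8, 0.5 and 0.3. Angle-on-velocity medians stayed within 0.05° of the true value, both here and for a 10° change.

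**Same threshold, different scatter.** With b = 0.02 and onset SD s, R² = b² × 9218.75/(b² × 9218.75 + s²), and b² × 9218.75 = 3.69.
- s = 1°: R² = 3.69/4.69 = 0.79, shift 0.9°.
- s = 2°: R² = 3.69/7.69 = 0.48, shift 3.5°.

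Doubling the scatter alone would appear as a TSRT change of about 2.6°.

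**Latency comparison.** Assume a true TSRT of 6° of plantarflexion, moving 0.02° further into plantarflexion per °/s, and a 35 ms latency. Ignore stretches without a reflex. The corrected onset angle is 6 + 0.02v. The uncorrected angle is 6 + (0.02 − 0.035)v = 6 − 0.015v. Both lines equal 6° at v = 0.

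Velocity-on-angle x-intercepts, in degrees of plantarflexion:
- s = 1°, corrected (R² 0.79): 9.25 − 3.25/0.787 = 5.1
- s = 1°, uncorrected (R² 0.67): 3.56 + 2.44/0.675 = 7.2
- s = 2°, corrected (R² 0.48): 9.25 − 3.25/0.480 = 2.5
- s = 2°, uncorrected (R² 0.34): 3.56 + 2.44/0.341 = 10.7

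The apparent effect of the correction on TSRT is 2.1° and 8.2°, where the true effect is zero. Simulation of the same cases gave 5.2, 7.1, 2.6 and 10.5. Angle-on-velocity gave 6.0 in all four.

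**The case against.** The strongest reply is that the article never says velocity is regressed on angle. Placing angle on the x-axis is a plotting choice. One can regress angle on velocity, draw that line on the same axes and read it at zero velocity, and every word of the section is satisfied without bias. The article also calls the calculation established and cites sources that are not at hand, and a condensed article may leave such detail elsewhere. This stands in part. A reader might infer that the plan prescribes the biased fit, and the text does not go that far. But the article does fix the plot, the intercept taken from the equation and the latency comparison, and together these lead an analyst most naturally to the biased direction.

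The size is also open to challenge. For the assumed changes of 5 to 10° the shift is below 1° at R² 0.9, and even a 15° change gives only 9.75 × 0.111 = 1.1°. Shifts of several degrees need poorer fits, and R² is to be obtained, so poor fits would be visible. That stands as a limit on size. The section attaches no consequence to a low R², however, and R² is the same for both directions of fit.

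A reader might think the shift depends only on R². It does not: it also scales with the slope and with the mean velocity of the stretches kept. At a fixed onset SD of 2°, it is 7.1, 3.5, 1.8 and 1.2° for changes of 2.5, 5, 10 and 15°.

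A reader might also set the Table 4 footnote, "positive values = dorsiflexion", against the statement that larger TSRT values mean more hyperreflexia and conclude that the sign is reversed. The documents do not support that. The footnote governs the flexibility table. For this dynamometer, Muscle strength and Electromyography express the ankle range as 0 to 28° into plantarflexion, and the TSRT stretch is described from plantarflexion to 0°. On that scale a larger threshold does mean more hyperreflexia.

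Finally, the latency correction leaves the zero-velocity intercept unchanged only if latency and stretch velocity are constant. A 20° stretch at 300°/s lasts about 67 ms (20/300 s), so a 35 ms look-back may reach into the acceleration phase. That qualification stands.

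**Conclusion.** The concern holds as an unfixed regression direction whose natural reading is the biased one. If velocity is regressed on angle by ordinary least squares, TSRT is shifted by |b| × 162.5 × (1 − R²)/R² with all stretches kept: about 0.4 to 0.7° at R² 0.9 and 3.3 to 6.5° at R² 0.5, for an assumed 5 to 10° change over 50–300°/s. The slope, scatter and R² are assumptions, since the article gives none of them, and discarded or non-responding stretches would alter the mean velocity.

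In that case the test of hypothesis k and the CP–TD comparison would partly reflect onset scatter. A bias in the change between visits arises only where scatter, slope or the retained velocities differ between them. The latency comparison would mix a real effect on slope and R² with an artefact in TSRT. TSRT is a secondary outcome, and the primary six-minute walk analysis is not touched.

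**What to change.** State that, for each muscle, DSRT angle is regressed on stretch velocity and that TSRT is the fitted angle at zero velocity, with slope and R² reported from the same fit. Add that, with constant latency and constant stretch velocity, the latency correction changes the slope and R² but not the zero-velocity intercept, so the planned discussion should concern the slope and R². The plot can keep its axes.

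The cost is a sentence or two of text and one line of analysis code. No new data are needed.
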